### Sample size calculations

2.6

The sample size calculation has been performed using R statistical software (R Core Team). In order to detect relevant differences between groups in the changes from pre-to post-intervention, we determined a sample size sufficient to detect medium effect sizes (Cohen’s *f* = 0.4). Therefore, α = 0.05, and *p* = 0.90, were selected to favor clinically significant effect sizes. The sample size calculation is based on sleep quality as the main variable. A total of 24 participants per group are necessary to examine the hypothesis that interventions impact sleep quality. Two additional participants are included to compensate for possible drop-outs. Each of the four groups will consist of 25 participants, resulting in a total of 100 participants.

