### Statistical analyses

2.7

Data will be analyzed with R statistical software (R Core Team, Austria). The statistical analysis will determine the effects of the three different training interventions on sleep, fitness, cognitive, and quality of life variables compared to a control group. The analysis will include subjects who completed all the pre-and post-tests. If participants drop out or deviate from the intervention protocols, their data will not be used. Deviations will include non-eligibility, withdrawal of consent, missed test visits, and intervention protocol not completed. Data from the pre-test and post-test will be presented using descriptive statistics: mean, standard deviation, and percentage to describe the participants’ characteristics and performance on assessments. Comparisons within and between four groups at baseline and post-intervention will be done using repeated measures ANOVA, after checking for normality. Assessments will be considered as the dependent variables, and the group will serve as the independent variable. *Post hoc* analyses will be conducted when a significant main effect is observed using Tukey’s test to correct for multiple comparisons.

The initial ANOVA, comparing the PET, PET, and BLE, control group, will aim to assess the presence of intervention effects (pre/post). The hypothesis is that the combined PET and light interventions will result in improved outcomes in both groups compared to the control group across various domains, including physical and motor fitness, cognitive, QoL, circadian rhythms, and sleep variables.

The second ANOVA, comparing the GVS and control groups, will be designed to assess the existence of intervention effects (pre/post). The hypothesis is that the GVS intervention will lead to improvements in balance, cognition, QoL, circadian rhythms, and sleep variables compared to the control group.

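### The 24 per group is sized for a four-group test at a large effect; 90% power is not assured for the planned three-group and two-group ANOVAs, and the drop-out allowance does not add up

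*Protocol article*

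**What the plan says.** Section 2.6 (Sample size calculations) places the effect on the change scale, "In order to detect relevant differences between groups in the changes from pre-to post-intervention", and names the outcome: "The sample size calculation is based on sleep quality as the main variable". The target is given as "we determined a sample size sufficient to detect medium effect sizes (Cohen’s *f* = 0.4". On error rates it says "Therefore, α = 0.05, and *p* = 0.90, were selected to favor clinically significant effect sizes"; the 0.90 can only be power. The result is "A total of 24 participants per group are necessary to examine the hypothesis that interventions impact sleep quality". It then says "Two additional participants are included to compensate for possible drop-outs" and ends at 25 per group, 100 in total.

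Section 2.7 (Statistical analyses) opens with a general sentence about repeated measures ANOVA within and between four groups, and then specifies two separate analyses, each with its own hypothesis. The initial ANOVA compares exercise (PET), exercise plus bright light (PET+BLE) and control. For the other, "The second ANOVA, comparing the GVS and control groups, will be designed to assess the existence of intervention effects (pre/post"). The same section drops the data of anyone who drops out, misses a test visit or does not complete the intervention.

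Section 2.3 (Assessments) puts the two GVS weeks after the 12-week follow-up and limits visit 4 to the GVS and control groups.

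**The concern.** The power statement should describe the tests that answer the trial's aims. Here the per-group number appears to belong to a test over all four groups, while the hypotheses are tied to a three-group and a two-group test. At the same f and the same number per group, an ANOVA with fewer groups has less power.

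Two further details point the same way. The effect is labelled medium although its numerical value is the conventional large one. The drop-out sum does not lead to the stated group size.

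GVS versus control is one of the trial's two declared aims. If that comparison is null, a reader of section 2.6 would take it as evidence, at 90% power, against a medium effect. The plan does not support that reading.

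**Working it through.** **Inputs.** From section 2.6: f = 0.4 on between-group differences in pre–post change, alpha = 0.05, power 0.90, n = 24 required and 25 enrolled per group. From section 2.7: k = 3 and k = 2 groups. No standard deviation, pre–post correlation or drop-out rate is given.

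**Formula.** With two time points, the group-by-time test is a one-way ANOVA on change. Power = P(F′ > F crit), where F′ is noncentral F with df1 = k − 1, df2 = k(n − 1) and noncentrality λ = k·n·f².

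**Step 1: reproduce the plan's figure.** For k = 4 and n = 24, λ = 4 × 24 × 0.16 = 15.36 with df 3 and 92, and power is 91.2%. At n = 23 it is 89.8%. The smallest n for 90% is therefore 24, as stated.

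**Step 2: the planned ANOVAs, with f = 0.4 within each.**

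| Test | λ at n = 24 | Power, n = 24 | Power, n = 25 | n per group for 90% | Detectable f at 90%, n = 24 |
|---|---|---|---|---|---|
| Four groups | 15.36 | 91.2% | 92.4% | 24 | 0.39 |
| PET, PET+BLE, control | 11.52 | 85.4% | 86.9% | 28 | 0.43 |
| GVS, control | 7.68 | 77.4% | 79.2% | 34 | 0.48 |

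**Step 3: f = 0.4 as the spread over all four groups.** Here f² is the mean squared deviation of the four group means, in units of the SD of change. The means are scaled so that f = 0.4, f is recomputed within each planned ANOVA, and power is taken at n = 24.

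- *All three interventions equal, control at 0.* Means 0, d, d, d give f = d × √(3/16), so d = 0.4 / 0.433 = 0.92. Within the ANOVAs, f = 0.92 × √(2/9) = 0.435 for three groups and 0.92 / 2 = 0.46 for two.
- *Equally spaced means.* Means 0, s, 2s, 3s give f = s × √1.25, so s = 0.4 / 1.118 = 0.358. The order of the arms then decides the result.

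| Pattern, lowest to highest | Three-group power | GVS versus control power |
|---|---|---|
| Control, then all three equal | 91% | 88% |
| Control, GVS, PET, PET+BLE | 92% | 23% |
| Control, PET, GVS, PET+BLE | 92% | 68% |
| Control, PET, PET+BLE, GVS | 58% | 95% |

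**Step 4: the label.** For two groups f = d/2, so f = 0.4 is d = 0.8. By the usual convention 0.25 is medium and 0.40 is large. At f = 0.25 and n = 24, power is 50%, 44% and 40% for four, three and two groups.

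**Step 5: the allowance.** 24 + 2 = 26 per group, or 26 × 4 = 104 in total. If the two are a total, 24 × 4 + 2 = 98. Neither gives 25 and 100. The actual margin is 25 − 24 = 1 per group, and 1/25 = 4%.

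The documents give no drop-out rate, so the next rows are assumed losses from 25, with f = 0.4 within each ANOVA.

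| Analysed per group | Loss | Three groups | Two groups |
|---|---|---|---|
| 25 | 0% | 87% | 79% |
| 24 | 4% | 85% | 77% |
| 22 | 12% | 82% | 74% |
| 20 | 20% | 78% | 69% |

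**Step 6: would baseline adjustment restore 90%?** ANCOVA replaces f² by f² × 2/(1 + r), where r is the pre–post correlation, and costs one error degree of freedom. The documents do not give r, so a range is shown at n = 24 with f = 0.4 on change within each ANOVA.

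| Assumed r | Three groups | GVS versus control |
|---|---|---|
| 0.5 | 94% | 88% |
| 0.7 | 91% | 84% |
| 0.8 | 89% | 82% |

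**The case against.** The strongest reply is that 24 is not a miscalculation. It follows exactly from the stated inputs for four groups, and section 2.7 does contain a sentence about comparing four groups. Both points are true. However, the two analyses that carry hypotheses have three and two groups. A pooled four-group pre/post test also fits the schedule poorly, because GVS is given only after week 12 and is assessed at visit 4 in two groups. The general sentence therefore does not make 91% the power of the planned tests.

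A second reply is that one f is given and its calculation fits four groups, so carrying 0.4 into each sub-comparison is the reviewer's choice. This stands in part. A reader might infer that the planned ANOVAs simply have 85% and 77% power, or that GVS faces more than twice the stated 10% false-negative risk. The document does not support either as a flat statement. Both hold if f = 0.4 applies within each ANOVA. Under the four-group reading power can be close to 90% for both tests, or well below it for either one. It can also exceed 90% for GVS if that is the strongest arm.

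Third, the label is a matter of convention, and the numerical f is printed for anyone to see. The power at f = 0.25 concerns an effect that the protocol never set as its numerical target. It shows only how far the word *medium* could mislead. The allowance slip is small: 25 per group and 100 in total agree throughout the article, so recruitment is unaffected.

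**Conclusion.** The point holds in conditional form. The stated 24 per group is right for a four-group omnibus test on change at f = 0.4, and section 2.6 gives no power for the three-group and two-group ANOVAs that section 2.7 specifies. With f = 0.4 within each, power is about 85% and 77% at 24 per group. With f = 0.4 as the four-group spread, it depends on the unknown pattern of means. On neither reading is 90% assured for either test.

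The effect is large by convention. The drop-out margin is one person per group, which is thin when section 2.7 excludes every drop-out and deviator.

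A reader might go further and conclude that the trial must enrol more participants, or that ANCOVA would put matters right without doing so. Neither follows. The shortfall depends on how f is defined, and at the correlations tried ANCOVA leaves GVS versus control at 82–88%.

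**What to change.** Rewrite the paragraph in section 2.6 so that it:

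- says that 24 per group refers to a four-group omnibus test on change;
- calls f = 0.4 a large effect;
- reports power or detectable effect for the two planned ANOVAs and states the assumption on f (if f = 0.4 holds within each: about 85% and 77% at 24 per group, 87% and 79% at 25, detectable f about 0.43 and 0.48 for 90% at 24), adding that under a four-group f the power depends on the pattern of means;
- gives the drop-out allowance as one participant per group (4%).

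No change in enrolment is proposed. If baseline-adjusted ANCOVA is adopted, present its gain over a range of pre–post correlations and do not describe it as restoring 90% for GVS. The cost is one reworded paragraph and less favourable stated figures.

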### Statistical analyses

2.7

Data will be analyzed with R statistical software (R Core Team, Austria). The statistical analysis will determine the effects of the three different training interventions on sleep, fitness, cognitive, and quality of life variables compared to a control group. The analysis will include subjects who completed all the pre-and post-tests. If participants drop out or deviate from the intervention protocols, their data will not be used. Deviations will include non-eligibility, withdrawal of consent, missed test visits, and intervention protocol not completed. Data from the pre-test and post-test will be presented using descriptive statistics: mean, standard deviation, and percentage to describe the participants’ characteristics and performance on assessments. Comparisons within and between four groups at baseline and post-intervention will be done using repeated measures ANOVA, after checking for normality. Assessments will be considered as the dependent variables, and the group will serve as the independent variable. *Post hoc* analyses will be conducted when a significant main effect is observed using Tukey’s test to correct for multiple comparisons.

The initial ANOVA, comparing the PET, PET, and BLE, control group, will aim to assess the presence of intervention effects (pre/post). The hypothesis is that the combined PET and light interventions will result in improved outcomes in both groups compared to the control group across various domains, including physical and motor fitness, cognitive, QoL, circadian rhythms, and sleep variables.

The second ANOVA, comparing the GVS and control groups, will be designed to assess the existence of intervention effects (pre/post). The hypothesis is that the GVS intervention will lead to improvements in balance, cognition, QoL, circadian rhythms, and sleep variables compared to the control group.

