### Study design

2.1

The study is a randomized controlled trial with four parallel groups: a Physical Exercise Training group (PET), a PET combined with Bright Light Exposure group (PET + BLE), a Galvanic Vestibular Stimulation group (GVS), and a control group [Health Education (HE)]. All participants will be provided written informed consent before their inclusion. The protocol has been approved by the local ethical committee (Comité de Protection des Personnes, CPP Nord Ouest III, Caen) in compliance with French regulations (trial registration number: IDRCB: 20206A01578-31). The researchers will provide participants with detailed written and oral information about the trial, ensuring voluntary participation and emphasizing that participants may withdraw at any time.

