### Assessments

2.3

Inclusion and randomization will occur at the baseline assessment (visit 1) and will involve the completion of pre-inclusion questionnaires. A pre-intervention visit will take place before the start of the intervention (visit 2) and a 12-week follow-up assessment will occur at the end of the 12-week intervention (visit 3) (Figure 1A). A final assessment will be performed after completion of the 14-week intervention, but only for control and GVS groups (visit 4) (Figure 1B). According to the literature, a typical GVS protocol is short and does not exceed 2 weeks (52). Therefore, the GVS protocol will be shorter than PET and BLE interventions to ensure participant feasibility and acceptability. The two weeks of vestibular stimulation will be scheduled after the 12-week follow-up to ensure consistent design (Figure 1B). The control group will be compared to the PET and PET + BLE group, but also to the GVS group.

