#### PET combined with bright light exposure (BLE)

2.4.2

Participants in the BLE group will receive the same remote exercise training intervention as the PET group. The PET intervention will be supplemented with 12 weeks of bright light exposure sessions at home. Each participant will be provided with a light lamp (DAYVIA^®^ 072, France) and will be instructed to self-administer light sessions 5 days a week (from Monday to Friday) for 1 h in the morning (between 8:00 am and 10:00 am). During the sessions, participants will face the 10,000-lux light box at a distance of 50 cm and 45° from the eyes, avoiding direct staring to minimize discomfort. The intervention will be remotely monitored on the SAPATIC digital platform, in specific: exposure days, exposure time, and remarks filled in by the participants.

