#### Control group-health education (HE)

2.4.4

The participants in the active control group will attend a one-hour health education session each week for a total of 14 weeks. These videoconference sessions will cover topics such as the benefits of physical activity, healthy lifestyles (including sleep habits and dietary balance), and cardiovascular risk factors. The inclusion of an active control group will aim to mitigate any potential influence of social contact and motivational factors on performance differences between the groups.

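### The only planned analysis set is adherent completers, so the groups compared are not the groups randomised and the estimates can be biased

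*Protocol article*

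**What the plan says.** Three consecutive sentences in the protocol article, Statistical analyses (2.7), define who is analysed. The first limits the set to people with a full series of assessments: "The analysis will include subjects who completed all the pre-and post-tests". The next removes everyone who stops early or departs from the assigned programme: "If participants drop out or deviate from the intervention protocols, their data will not be used". The last lists what counts as such a departure, and it mixes eligibility with events after allocation: "Deviations will include non-eligibility, withdrawal of consent, missed test visits, and intervention protocol not completed".

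The Study design section states that "The study is a randomized controlled trial with four parallel groups", and the Assessments section that "Inclusion and randomization will occur at the baseline assessment (visit 1"). The pre-test (visit 2), the interventions and the post-tests (visit 3 for all groups, visit 4 for GVS and HE only) all come later. The article contains no analysis of all randomised participants, no method for missing data and no sensitivity analysis.

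What a participant has to complete depends on the arm. PET is two supervised sessions and one self-guided session a week for 12 weeks. PET+BLE participants do the same and also "self-administer light sessions 5 days a week (from Monday to Friday") for 12 weeks. GVS is five sessions a week for two weeks. HE participants "attend a one-hour health education session each week for a total of 14 weeks".

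**The concern.** Dropping out, missing a visit and not finishing the programme all happen after allocation and can be caused by it. Removing people on these grounds undoes the balance that randomisation provides, so a difference between the remaining groups may partly reflect who was able or willing to finish.

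The opportunity to fail differs by arm. The session counts are far apart, and the adverse effects listed under Data collection and management differ too: muscle pain, cardiovascular problems and falls for PET; headache, eye strain and nausea for BLE; nausea and dizziness for GVS. The Discussion itself expects the length of the protocol to discourage some participants.

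The trial is meant to inform recommendations on home programmes for older adults. For that purpose the effect of being assigned to a programme matters, and non-completion is part of that effect. The rule governs every comparison and every outcome.

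**Working it through.** **1. Planned sessions per arm** (Interventions, 2.4)

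- PET: (2 + 1) × 12 = 36
- PET+BLE: 36 + 5 × 12 = 96
- HE: 1 × 14 = 14
- GVS: 5 × 2 = 10

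PET and PET+BLE carry much more than HE. GVS carries fewer sessions than HE.

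**2. Size of the bias.** Let e₁ and e₀ be the shares excluded in the active and control arms. Let g be the mean outcome of completers minus that of non-completers, in SD units, taken as equal in both arms. The completer mean exceeds the full-arm mean by e × g, so

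bias = (e₁ − e₀) × g.

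The documents give none of these values, so the following are assumptions:

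| e₁ | e₀ | g (SD) | bias (SD) |
|---|---|---|---|
| equal to e₀ | any | any | 0 |
| any | any | 0 | 0 |
| 0.20 | 0.05 | 0.5 | 0.15 × 0.5 = 0.075 |
| 0.30 | 0.05 | 0.8 | 0.25 × 0.8 = 0.20 |

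A second approach sets the true effect to zero, keeps all 25 controls, and lets non-completion in one active arm follow a latent normal variable with correlation ρ to the change score. Then bias = ρ φ(z_d) / (1 − d) for an excluded share d. The type I error was obtained by simulation (two-sided 5% t-test, 25 controls against 22, 20 or 18 completers).

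| d | bias, ρ = 0.3 to 0.5 (SD) | type I error, ρ = 0.3 to 0.5 |
|---|---|---|
| 10% | 0.06 to 0.10 | 0.055 to 0.062 |
| 20% | 0.11 to 0.18 | 0.064 to 0.088 |
| 30% | 0.15 to 0.25 | 0.074 to 0.125 |

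At ρ = 0 the bias is nil and the type I error stays at about 0.05. The two approaches agree in order of magnitude.

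**3. Power.** The Sample size calculations section (2.6) uses f = 0.4 and states: "Therefore, α = 0.05, and *p* = 0.90, were selected to favor clinically significant effect sizes". The 0.90 is read here as power. For a one-way ANOVA with k groups of n, N = kn, the noncentrality is λ = f²N and the degrees of freedom are (k − 1, N − k).

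The plan's own figure comes first. With k = 4 and n = 24, λ = 0.16 × 96 = 15.36 and power is 0.912, so 24 per group reproduces.

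The ANOVAs actually planned have three groups (PET, PET+BLE, control) and two groups (GVS, control). A 20% loss leaves 25 × 0.8 = 20 per group.

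| Comparison | n = 25, none excluded | n = 20, 20% excluded | Loss |
|---|---|---|---|
| k = 3 | 0.869 (λ = 12.0) | 0.776 (λ = 9.6) | 0.093 |
| k = 2 | 0.791 (λ = 8.0) | 0.693 (λ = 6.4) | 0.098 |

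The built-in reserve is 25 − 24 = 1 per group (4%), although the same section speaks of two additional participants.

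**The case against.** The strongest defence is that none of the harm is demonstrated. No drop-out rate by arm is given, and nothing in the documents links stopping to outcome. The Discussion cites better adherence through videoconferencing, and allowances are paid to keep people in. This stands as a limit on size and direction. It does not rescue the rule, which is stated outright: an unseen analysis plan that kept all randomised participants would contradict it.

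A reader might go further than the documents allow in four ways.

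- **That the bias certainly favours the active arms.** It does so only if non-completion is linked to poorer response and differs between arms. The session-count argument fails for GVS (10 sessions) against HE (14), where the control has more to complete.
- **That the rule alone reduces power to 78% and 69%.** With nobody excluded, power is already 87% and 79%, because 24 per group fits a four-group test that is not the one planned. A 20% loss costs 9-10 points. The rest of the gap from 90% is a separate sample-size matter.
- **That HE participants who leave between weeks 12 and 14 are lost from the PET comparison.** This follows if completion is judged over the whole study, but the text does not say whether it is judged overall or per comparison.
- **That a few missed sessions lead to exclusion.** The article sets no threshold for an uncompleted intervention, so session totals indicate exposure to the rule, not exclusion rates.

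It is also fair to say that removing people who were ineligible on criteria fixed before randomisation is less harmful than the other exclusions. The rule does not separate them.

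**Conclusion.** The rule is wrong as written. It makes adherent completers the only analysis set and discards all data from everyone else on grounds that arise after randomisation and can depend on the arm. The groups compared are therefore not the randomised groups, and the estimates can be biased: probably upward for PET and PET+BLE if people who stop respond less well, in an uncertain direction for GVS against HE, and not at all if stopping is unrelated to outcome.

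The size rests on assumptions. It is zero with equal exclusion or no outcome gap, and about 0.08-0.20 SD under the exclusions and gaps assumed in the first table. The added cost in power at 20% loss is 9-10 percentage points in each planned ANOVA. The defect itself needs no assumption, since it lies in the stated rule, and it should be corrected before outcome data are seen.

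**What to change.** Replace the three sentences so that the main analysis includes all randomised participants in their allocated group, whatever their adherence, outcome by outcome and with all available data. Then:

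- Attempt visit 3, and visit 4 for GVS and HE, in people who stop the intervention and still consent. Most of the gain comes from this and from keeping non-adherers' data, because PET and PET+BLE have only one post-intervention visit.
- Use a likelihood-based mixed model with baseline and post-intervention values as the repeated outcomes, and state the missing-at-random assumption. If baseline were a covariate instead, anyone in PET or PET+BLE who misses visit 3 would contribute nothing.
- Treat ineligibility on pre-randomisation criteria separately and apply it identically in all arms that are compared. This needs care because, under Assessments, the visit 2 VO2 peak test that can lead to exclusion is not done in GVS.
- Keep the completer analysis as a labelled sensitivity analysis.

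Recruiting more people is no substitute. Keeping 24 completers at 20% loss would take 24 / 0.8 = 30 per group, which would restore precision but not comparability.

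The cost is a change of wording, some effort to follow up people who stop at visits already scheduled, and an estimate that may be slightly less favourable.

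### Section 2.7 states a four-group post-intervention ANOVA that the visit schedule does not support and that conflicts with the two ANOVAs named after it; the GVS-versus-control verdict can depend on which is run

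*Protocol article*

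**What the plan says.** Section 2.7 (Statistical analyses) opens its inferential plan with "Comparisons within and between four groups at baseline and post-intervention will be done using repeated measures ANOVA, after checking for normality". The post hoc rule follows, without restriction to any model: "analyses will be conducted when a significant main effect is observed using Tukey’s test to correct for multiple comparisons".

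The next two paragraphs name two models. The first is "The initial ANOVA, comparing the PET, PET, and BLE, control group, will aim to assess the presence of intervention effects (pre/post", which I read as PET, PET+BLE and control. The second is "The second ANOVA, comparing the GVS and control groups, will be designed to assess the existence of intervention effects (pre/post". Each has its own hypothesis against control.

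Section 2.3 (Assessments) sets the visits. For the 12-week programmes, "a 12-week follow-up assessment will occur at the end of the 12-week intervention (visit 3". For GVS, "The two weeks of vestibular stimulation will be scheduled after the 12-week follow-up to ensure consistent design", and "A final assessment will be performed after completion of the 14-week intervention, but only for control and GVS groups (visit 4". The same section summarises the intended comparisons: "The control group will be compared to the PET and PET + BLE group, but also to the GVS group".

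Section 2.6 gives 24 per group for f = 0.4, α = 0.05 and 0.90 (printed as p, read here as power), and enrols 25 per group.

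**The concern.** The opening sentence and the two named ANOVAs are different tests of the same endpoints. A four-group model has six pairwise contrasts and pools its error over four arms. The named models have three contrasts and one, each with its own error term. No sentence gives either plan precedence.

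The four-group comparison also needs a post-intervention value common to all arms, and the schedule does not provide one. If the sentence stays, an analyst can choose the model after seeing the data. For a GVS-versus-control difference of moderate strength, that choice can settle whether it is called significant.

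**Working it through.** **1. Visits.**

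| Arm | Post-intervention visit | Week |
|---|---|---|
| PET | 3 | 12 |
| PET+BLE | 3 | 12 |
| GVS | 4 | 14 |
| Control | 3 and 4 both available | 12, 14 |

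At visit 3 the GVS arm has had no stimulation. At visit 4 the exercise arms are not assessed. A four-group post-intervention factor would therefore set GVS at week 14 against exercise at week 12, with the control visit undefined. For VO2 peak it cannot be formed at all, because section 2.3 does not measure it in the GVS arm.

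**2. The plan's own sample size.** One-way ANOVA with k groups of n: noncentrality λ = k·n·f², degrees of freedom k−1 and k(n−1), f = 0.4, α = 0.05.

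- k = 4, n = 24: λ = 4 × 24 × 0.16 = 15.36, power 91.2%. At n = 23 power is 89.8%. So n = 24, which reproduces the stated figure.
- k = 3: 90% power needs n = 28. At n = 25, λ = 12.0 and power is 86.9%; at n = 24 it is 85.4%.
- k = 2: 90% power needs n = 34. At n = 25, λ = 8.0 and power is about 79%; at n = 24 it is 77.4%.

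The stated 24 fits four groups and neither of the two named ANOVAs.

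**3. GVS versus control under each model.** Assumptions: 25 per arm all analysed, equal-variance change scores, d on the change-score scale; for two groups d = 2f = 0.8.

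- Two-group ANOVA: critical |t| = t(0.975; 48) = 2.011.
- Four-group Tukey: q(0.95; 4, 96)/√2 = 2.615, equivalent to an unadjusted p of about 0.010.
- Noncentrality at d = 0.8: 0.8 × √(25/2) = 2.83.

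| True d | Power, two-group | Power, four-group Tukey |
|---|---|---|
| 0.5 | 41.0% | 20.5% |
| 0.6 | 54.7% | 31.6% |
| 0.8 | 79.1% | 58.6% |
| 0.9 | 87.7% | 71.4% |
| 1.0 | 93.4% | 81.9% |

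Requiring a significant overall F before Tukey, as section 2.7 does, lowers 58.6% to 58.2% (100,000 simulated trials). At d = 0.8 the two models disagree in 20% to 21% of simulated trials, with or without that gate. With no GVS effect, GVS versus control is falsely significant in about 5% of trials against 1%.

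**4. PET versus control.** Three-group Tukey: q(0.95; 3, 72)/√2 = 2.393, power 67% at d = 0.8. Four-group Tukey: 2.615, power 59%.

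**5. Error over both named ANOVAs.** With the shared control arm, simulation under the null gives about 9.1% for at least one false positive per endpoint, against about 5% for four-group Tukey. If the two ANOVAs were independent it would be 1 − 0.95² = 9.75%.

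**The case against.** The best defence is that the four-group sentence only names the method and the two ANOVAs carry it out. Much of this stands. The initial and second ANOVA are listed straight after the method, each has a hypothesis, no four-group hypothesis appears, and section 2.3 describes the same two comparisons with control. The two named ANOVAs are the more natural plan.

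It does not clear the text. Comparing between four groups includes GVS against each exercise arm, which no aim asks for. Tukey adds nothing to a two-group ANOVA, yet the rule is unrestricted. The stated 24 per group reproduces only with four groups. Section 2.6 does not say how many groups it used, so that match is evidence and not proof. Visit coding may well sit in an unseen analysis plan, but here the published sentence states a comparison that the schedule contradicts.

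Four stronger readings are tempting and unsupported:

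- That GVS could be scored at visit 3, so that no effect could appear. Section 2.3 places stimulation after that visit, so visit 3 is not post-intervention for GVS.
- That a four-group model cannot be computed. It can, with arm-specific post visits, but arm is then confounded with week.
- That the GVS verdict always turns on the model. At d = 0.8 the models agree in about 79% of trials.
- That 9% per endpoint is an error. The two ANOVAs serve two stated aims, and control per aim is a common choice; it only needs saying.

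**Conclusion.** The four-group post-intervention sentence in section 2.7 is wrong as written and should go; the two named ANOVAs fit the aims and the schedule. The GVS-versus-control verdict can depend on the model: critical |t| is 2.01 against 2.61, power at d = 0.8 about 79% against 58–59%, and about 20% of trials give opposite verdicts, mainly those with p between about 0.01 and 0.05. Outside that band the models largely agree.

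These figures assume all 25 per arm are analysed. Section 2.7 keeps completers only, so actual power would be lower under either model; at 24 per arm it is 77.4% against 56.3%. The pre/post correlation is not given; any gain from it applies to both models.

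The correction reaches section 2.6, whose 24 per group at 90% power does not belong to the two ANOVAs. This is a point to settle before analysis, not a flaw in the design.

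**What to change.** In section 2.7:

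- Delete the four-group post-intervention test. Keep pre-test and post-test descriptive statistics for all groups.
- State that the two named ANOVAs are the only inferential models.
- For PET, PET+BLE and control, use visit 2 to visit 3. For GVS and control, use visit 4 as the post visit, with one stated pre visit (2 or 3) applied to both arms.
- Limit Tukey to the three-group ANOVA, and state that GVS is not tested against PET or PET+BLE.
- State that the 5% level holds per ANOVA, which is about 9% per endpoint over both.

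In section 2.6, restate the calculation for the models that will be run. With 25 per arm and f = 0.4, power is about 87% for the three-group ANOVA and 79% for GVS versus control; 90% would need 28 and 34 per group.

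The cost is wording in two sections, with no new data or participants if 25 per arm is kept. The trial gives up GVS-versus-exercise contrasts, which no aim requires, and must report a less favourable power.
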